Recent advances in molecular microbiology and bioinformatics including next-generation sequencing have enabled direct and deep sequencing of bacterial DNA from stool samples of neonates to describe the gut microbiome, identify dysbiosis, and investigate its impact on the risk of developing sepsis and AMR transmission. The aim of this study is to analyze maternal and neonatal gut microbiome and the risk to develop LOS or NEC. This collaborative academic partnership study is, to our best knowledge, the first to examine the gut microbiome of preterms in Tanzania.

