### Research questions

Our primary research question aims to answer whether gut dysbiosis precedes the development of LOS and/or NEC in Tanzanian preterm neonates and whether microbial or metabolomic markers predict neonates at high risk. Secondary research questions include 1) What are the maternal and neonatal risk factors for LOS and/or NEC? 2) What are factors associated with disease severity and outcomes? 3) What bacteria species and AMR profiles are found in blood culture isolates of preterm neonates with LOS and/or NEC?

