## Materials and methods

### Study design

This study will be a case-control study nested into a hospital-based, single-center, observational neonatal cohort. Recruited preterm neonates will be followed over their first 28 days of life. The primary clinical endpoint in this study is a blood culture (BC)-proven LOS. Secondary endpoints are clinical sepsis, NEC, death to clinical and/or BC-proven sepsis or NEC, death to any cause, or discharge from the hospital with or without sequelae.

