The calculations are based on formulae 1 for a two-sample proportions test, where *n*_*i*_ is the sample size estimated for each group, z is the normal deviation defined for the alpha level (α) and the study power (β), and *p*_*i*_ is the proportions in the respective groups.

$$n_{i}=\frac{{\left(Z\alpha /2+Z1-\beta \right)}^{2}*(p1(1-p1))+(p2(1-p2))}{{\left(p1-p2\right)}^{2}}$$
(formulae 1)

These parameters define minimal study numbers to reach power and significance. We aim to include all cases of LOS and NEC with complete microbiome and a higher number of controls, to improve the statistical power of the study, precision of the applied data analysis and allow potential subgroup analyses [19].

In the literature, the rate of positive BCs varies between study sites and is highly dependent on the quality of diagnostic procedures as well as the amount of blood transferred into BC bottles. Based on the available data and our experiences we are expecting to screen 80–100 admissions per month in the respective GA range and a study inclusion rate of 50–75%. Thus, we expect to recruit approximately 40–75 admitted newborns per month for a period of 18 months, which amounts to 720–1350 admissions over the study period. The calculations were enforced by comparing data from previous studies [7,24] and the ongoing NEST360 survey in the NCU [25], powered to identify sepsis incidence, risk factors, and mortality rates of LOS and NEC among preterm neonates.

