### Definitions of LOS, culture proven sepsis, clinical sepsis and NEC

LOS is defined as a bloodstream infection occurs after 72 hours of life, typically caused by nosocomial or community-acquired pathogens [26]. Culture-proven sepsis is identified when a bacterial or fungal pathogen is isolated from a sterile site, such as blood or cerebrospinal fluid. In contrast, clinical sepsis is diagnosed based on clinical signs and symptoms consistent with sepsis in the absence of a BC [27]. The signs and symptoms of neonatal sepsis range from nonspecific manifestations to hemodynamic collapse, requiring a high index of suspicion for timely diagnosis. This study will uniformly apply the WHO criteria for neonatal sepsis, which offer a standardized approach for identifying sepsis in preterm neonates [28]. LOS will be defined by the following criteria by responsible physicians, at least the presence of two signs as per WHO which includes difficulty feeding, convulsions, lethargy, tachypnoea, severe chest indrawing, hypothermia, hyperthermia, bulging anterior fontanelle and skin or umbilical infection with pus requiring systemic antibiotics for at least five days [28].

Cases will be categorized as culture-proven sepsis and clinical sepsis. Instances of positive BCs without accompanying signs or symptoms will be considered contaminants. Specifically, coagulase-negative staphylococci (CoNS) will be classified as a pathogen only if overt signs and symptoms consistent with sepsis, as defined by WHO criteria, are present; otherwise, CoNS will be regarded as contaminants [29]. To improve diagnostic accuracy where available, C-reactive protein (CRP) levels will be used as a biomarker during suspected sepsis episodes, with elevated levels supporting the presence of an inflammatory response [30].

In this study, NEC is defined and suspected clinically based on the presence of one or more of the most characteristic clinical features including abdominal distension, feeding intolerance, bilious vomiting or gastric aspirate and bloody stools, and if available, complemented by the finding on abdominal imaging of intramural gas, pneumoperitoneum or sentinel bowel loops [31,32].

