Antibiotic interventions following a LOS diagnosis are likely to have a strong impact on the microbiome composition. Statistical analyses will be performed using the latest version of R statistical software. Cox regression will be calculated using the *survival* package and LME using the *lme4* package. In all above-mentioned association tests, samples taken after LOS diagnoses will be excluded from the statistical analysis since the present study focusses on the microbial pattern that precedes LOS.

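### The rule that removes post-event stool samples names LOS only, although NEC belongs to the primary microbiome question and infants with NEC may serve as controls

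*Protocol article*

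**What the plan says.** NEC stands beside LOS in three places of the protocol article. The Introduction states: "The aim of this study is to analyze maternal and neonatal gut microbiome and the risk to develop LOS or NEC". Under Research questions, the primary question is "whether gut dysbiosis precedes the development of LOS and/or NEC in Tanzanian preterm neonates". Under Study population and sample size, the intention for the microbiome comparison is: "We aim to include all cases of LOS and NEC with complete microbiome and a higher number of controls".

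The Statistical analysis section is narrower. Its mixed model for species abundance has gestational age, days of life, diet and LOS as factors, and no term for NEC. The exclusion rule reads: "In all above-mentioned association tests, samples taken after LOS diagnoses will be excluded from the statistical analysis". Two reasons are given, and both name only LOS: "Antibiotic interventions following a LOS diagnosis are likely to have a strong impact on the microbiome composition", and the rule applies "since the present study focusses on the microbial pattern that precedes LOS".

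Three other statements matter:
- **Controls** (Study population and sample size) must have no clinical or culture-proven sepsis after 72 hours of life. Freedom from NEC is not required.
- **NEC** has its own definition: "NEC is defined and suspected clinically based on the presence of one or more of the most characteristic clinical features". The LOS criteria ask for at least two signs from a WHO list.
- **Stool** is collected on days 1–3, 7, 14 and 21 (each ±3), whatever events occur.

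**The concern.** A question about what precedes NEC cannot be answered with samples taken after NEC has begun. The article's own reason for dropping post-LOS samples, that antibiotics change the microbiome, carries over to NEC: the Blood cultures section treats signs of LOS and of NEC alike and expects antimicrobial treatment not to be delayed in either. The bowel disease and interrupted feeding may also alter the stool.

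Two results are at stake. One is any comparison of NEC cases with other infants. The other is the LOS comparison itself, since infants treated for NEC can stand among the controls.

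**Working it through.** **1. Does any text remove post-NEC samples?** No. The rule in the Statistical analysis section is the only post-event exclusion in the article, and its trigger is a LOS diagnosis.

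**2. Can NEC occur without LOS?** Yes, under the article's definitions. One abdominal feature is enough for NEC, whereas LOS needs a bloodstream infection or, on the second wording in the definitions section, two WHO signs. The bowel features (distension, bilious vomiting or aspirate, bloody stools) are not on the WHO list. Some infants with NEC will also meet the sepsis criteria. They then cannot be controls, and their samples after a LOS diagnosis are already dropped. The gap is therefore NEC without LOS, plus the interval between NEC and a later LOS.

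**3. How many samples per infant?** With nominal days 2, 7, 14 and 21 and no LOS:

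| NEC onset | Samples after onset | Share |
|---|---|---|
| day 5 | 7, 14, 21 | 3/4 = 75% |
| day 10 | 14, 21 | 2/4 = 50% |
| day 16 | 21 | 1/4 = 25% |
| after the last sample | none | 0% |

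The ±3-day windows, missed samples, death and discharge shift these counts.

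**4. Direction of the effect.** It depends on where the infant with NEC but no LOS is placed.
- *As a case in a NEC (or combined LOS/NEC) comparison:* post-NEC samples are read as preceding NEC. Consequences of the disease and its treatment then create or inflate an association.
- *In the specified LOS model, or as a control:* the infant is on the non-LOS side. Disturbed post-NEC samples make that side look more dysbiotic and shrink the LOS contrast.

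**5. The plan's own figure.** Inputs from the sample size section: dysbiosis 30% without and 60% with LOS, alpha 5% (two-sided, from Zα/2), power 80%. With pooled variance, p̄ = 0.45:

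n = [1.960·√(2·0.45·0.55) + 0.842·√(0.30·0.70 + 0.60·0.40)]² / 0.30² = (1.379 + 0.565)² / 0.09 ≈ 42 per group, 84 in all.

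This reproduces the stated 84; power at 42 per group is 80.0%.

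**6. Illustration of dilution (assumed inputs).** Let a share f of controls be classified on post-NEC samples, and let those be dysbiotic with probability q. The control proportion becomes p_c = (1 − f)·0.30 + f·q, and

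power = Φ{[(0.60 − p_c)·√n − 1.960·√(2p̄(1 − p̄))] / √(p_c(1 − p_c) + 0.24)}, with p̄ = (p_c + 0.60)/2.

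For f = 5%, q = 0.6: p_c = 0.95·0.30 + 0.05·0.6 = 0.315, and power at n = 42 is 75.5%.

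| f | p_c (q = 0.6 to 1.0) | Power, 42 per group | Power, 54 per group |
|---|---|---|---|
| 0 | 0.300 | 80.0% | 89.1% |
| 2% | 0.306–0.314 | 78.3–75.8% | 87.7–85.7% |
| 5% | 0.315–0.335 | 75.5–68.8% | 85.5–79.7% |
| 10% | 0.330–0.370 | 70.6–56.1% | 81.2–67.1% |

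The 54 is the lower end of the complete stool sets that the article expects (720 × 10% × 75% = 54). Neither f nor q is given in the article. The calculation uses the two-proportion test of the sample size section, not the mixed model.

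**The case against.** The best defence is that the Statistical analysis section is coherent in itself. It specifies a LOS model, applies a LOS exclusion to it, and says that LOS is the focus. BC-proven LOS is the primary clinical endpoint, and NEC is a secondary one: "Secondary endpoints are clinical sepsis, NEC, death to clinical and/or BC-proven sepsis or NEC". No NEC microbiome model is written out, and a fuller protocol or SAP may contain one. This stands as far as it goes: reverse causation for NEC is conditional on NEC cases being compared under this rule. It does not remove the mismatch, because the aim, the primary question and the case set all name NEC, and the control definition lets infants with NEC in.

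A reader might draw four stronger conclusions, which the article does not support.
- *That the LOS association would itself be produced by reverse causation.* In the specified model the post-NEC samples of infants without LOS lie on the non-LOS side, so the expected effect is dilution.
- *That a sample taken between NEC and a later LOS is misclassified.* With NEC on day 8 and LOS on day 20, the day 14 sample does precede LOS. Earlier NEC is a possible confounder or a step on the path to LOS. Matching on previous antibiotic exposure and type of feeding already addresses part of this, though not NEC's own effect.
- *That samples after clinical sepsis are kept as well.* This follows only from the opening definition of LOS as a bloodstream infection. The same section goes on to define LOS by clinical signs and to divide cases into culture-proven and clinical sepsis; on that reading those samples are already removed.
- *That the number of affected infants can be stated.* An assumed NEC rate of 3–7% would give 720 × 0.03 ≈ 22 to 1350 × 0.07 ≈ 95 infants. The rate is not in the article, and the count ignores infants who also have LOS, the 25% missed samples, and NEC after the last stool.

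**Conclusion.** The mismatch is real and lies in the current text. NEC is in the aim, the primary research question and the microbiome case set, but the post-event exclusion is triggered by LOS alone and controls may have NEC. Followed as written, the rule keeps samples taken after NEC and its treatment.

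The consequence has two parts: reverse causation in any NEC comparison made under the rule, and some dilution of the specified LOS contrast. The size of either cannot be computed without a NEC rate. The power losses shown are illustrations that depend on assumed f and q, and the larger number of controls that the article intends would change them. The stated sample size of 84 is not affected. The point should be settled before the analysis begins.

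**What to change.** In the Statistical analysis section, extend the exclusion rule:

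1. Exclude samples taken after a NEC diagnosis from any comparison in which NEC is the outcome or part of it.
2. State that infants with NEC either do not serve as controls or contribute only samples taken before NEC. Apply the same to the non-LOS side of the mixed model.
3. For infants with NEC followed by LOS, keep the samples between the two events in the main LOS analysis and drop them in a sensitivity analysis.

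Alternatively, limit the primary microbiome question and the case set to LOS, so that they match the model and rule already written. Infants with NEC among the controls should still be handled as in item 2.

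The cost is a few sentences of text, with no new data collection, since episodes of NEC and sample collection are already recorded in the eCRFs. Some samples from infants with NEC are lost. Because a single feature is enough for NEC, the loss may not be trivial. This is a reason not to cut every infant's samples at first suspected NEC in the main LOS analysis. Extending the rule does not supply a NEC model; if one is intended, it has to be specified as well.

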### Study population and sample size

The study participants will include inborn and outborn preterm neonates born at 28 + 0 to <34 weeks of GA admitted to the neonatal wards, and their respective mothers who consented to participate after a detailed description of the study has been given by trained study team members. Recruited preterm neonates should have a minimal weight of at least 1000 g and be enrolled within their first week of life. We will exclude infants whose mothers are below 18 years of age, have severe, life-threatening illness at the time of admission, and/or have severe comorbidities or severe congenital malformations. Furthermore, neonates or mothers who ever received probiotic supplements during pregnancy will be excluded from this study.

Sample size calculations considered all study objectives and the one requiring the largest sample size will be the basis to determine recruitment numbers. All eligible preterm neonates admitted to the neonatal unit during the 18-month study period will be recruited and closely followed up for 28 days each.

To answer the primary research question on the hypothesis of preterm neonates developing gut dysbiosis before the onset of sepsis we need to identify preterms with BC-proven sepsis, assess their microbiomes, and compare it with controls (matched for GA, sex, mode of delivery, type of feeding, and previous antibiotic exposure). Assuming a rate of BC-proven sepsis of 10% and 25% missed samples we expect to identify 72–135 bloodstream pathogens (positive BCs) with 54–101 complete sets of stool samples for microbiome analysis within 18 months [7,10]. According to Graspeuntner *et al.,* we then expect gut dysbiosis in 30% of the neonates without and 60% of the children with LOS [19].

Our minimal sample size considerations are based on the proportions of gut dysbiosis in children with and without LOS. Assuming an alpha level of 5% and a power of 80% a minimal study number of 84 children (42 with and 42 without LOS) is needed to reject the null hypothesis that no difference in the proportion of dysbiosis between both cases and controls. Cases are defined as preterm neonates who develop LOS and controls as preterm neonates who do not develop any clinical or culture proven sepsis during the observation period (after 72 hours of life).

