### Variables to predict LOS and gut dysbiosis

Variables have been selected based on a literature search and local clinical experience. Table 1 shows factors predicting LOS and gut dysbiosis that will be captured during the study period. Independent variables will be categorized as socio-economic, neonatal, maternal, and septic risk factors (Table 1).

**Table 1 pone.0325099.t001:** Candidate variables for predicting LOS and gut dysbiosis.

Socio-economic factors	Neonatal factors	Maternal factors	Septic risk factors
Maternal education level	Gestational age	Age at delivery	Invasive ventilation
Self-rated household income	Sex	Parity	Central line at least 48 hrs
Family health insurance	Birth weight	Previous stillbirths	Parenteral nutrition
	Multiple births	HIV status	Presence of any maternal risk factors
	APGAR score at 1 minute	Medical conditions	Type of feeding
	APGAR score at 5 minutes	Pregnancy complications	
	Place of birth	Maternal antibiotic exposure 3 months before delivery	
	Delivery complications		
	Antibiotic exposure and type		
	Type of delivery		

During the observational period of 28 days clinical signs and symptoms of LOS and/or NEC, BC results with phenotypic identification, and antibiotic susceptibility testing, the previous use and type of antibiotics, and the clinical outcomes, will be recorded by the study team in electronic data capture forms. Stool samples for microbiome analysis will be collected in a standardized manner on day 1–3, and days 7, 14, 21 (each ±3) and neonates’ type of feeding in the last 24 hours will be categorized as exclusive human milk (no formula given), breastfed mainly (>80% feeds breastmilk/human milk), formula feed (>50% of feeds include formula), only formula (no human milk), or no enteral feeding at all.

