#### Isolation and identification.

BC bottles that have been inoculated will be sent to the laboratory as soon as possible by the study nurses, or stored at ambient temperatures if transport to the lab is delayed. Once BC bottles are received in the microbiology laboratory, registration follows whereby BC bottles are given the unique ID number and loaded into the automated BACTEC^®^ system (BACTEC® 9050; Becton Dickinson) for incubation and monitored for a maximum of five days to observe bacteria growth. For each positive BC, a primary gram stain will be performed and communicated to the clinician as soon as possible. Organisms will be sub-cultured on Blood Agar (BA), MacConkey (MCA, Oxoid, UK), and or Sabouraud Dextrose Agar (SDA) if the primary gram stain observed the presence of budding yeast cells microscopically. Organisms will be identified based on their colonial morphology and biochemical characteristics as described by Murray et al. (30). Gram-negative organisms will be identified using oxidase, Kliger Iron Agar (KIA), sulfur indole and mobility (SIM), a urease, and citrate test, while gram-positive organisms will be detected by catalase reaction, coagulase test, DNase test, and bile esculin test (30). Analytical Profile Index (API) 20E and API-20 NE (BioMérieux, France) tests will be used to confirm isolates in case of ambiguity.

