### Statistical analysis

Descriptive statistics will be used to summarize the demographic and clinical characteristics of the study population, including gestational age, birth weight, gender, mode of delivery, and presence of comorbidities. Mean and standard deviation or median and interquartile range for continuous variables will be used and for categorical data frequencies or proportions will be described.

To answer the first objective on the incidence and risk factors of LOS, the incidence density will be calculated as the number of new cases of LOS divided by the total person-time at risk in the cohort. The person-time at risk will be calculated by summing the individual follow-up durations until the occurrence of BC-proven LOS (clinical sepsis, NEC, and death).

Cox-proportional hazard regression will be utilized to investigate the relationship between the risk factors and risk to develop primary and secondary endpoints. First, we will perform univariate cox-regressions for potential risk factors to identify individual risk factors, all variables considered relevant for the study question will be included in the multivariate cox-regression to adjusting for potential confounders. The hazard ratios (HRs) with the 95% confidence intervals (CIs) will be estimated for each risk factor. Etiological agents of LOS/NEC and the respective AMR patterns will be described as the proportion of isolates resistant to each antibiotic and according to international standard.

Microbiome analysis will be performed to evaluate gut dysbiosis in preterm infants prior to the development of LOS and in relation to the microbiome of the mother. Association of relative abundances of microbial species with the factors of gestational age, days of life, diet, and LOS will be limited to species that were found with a non-zero relative abundance in at least 40 stool metagenomes. Square root-transformed relative abundancies will be used and analysed using linear mixed effect (LME) models, where repeatedly collected microbiome data from each child is considered to cluster.

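### The pre-LOS cut-off shortens only the cases' stool series and controls have no index age, so the per-child dysbiosis contrast and the matching on time-varying factors are not like for like

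*Protocol article*

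**What the plan says.** All references are to the protocol article.

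- **Statistical analysis:** when associations are tested, the plan is that "samples taken after LOS diagnoses will be excluded from the statistical analysis since the present study focusses on the microbial pattern that precedes LOS". No parallel cut-off is given for controls. The same section relates species abundances to several factors ("Association of relative abundances of microbial species with the factors of gestational age, days of life, diet, and LOS") using "linear mixed effect (LME) models, where repeatedly collected microbiome data from each child is considered to cluster".
- **Study population and sample size:** controls are "matched for GA, sex, mode of delivery, type of feeding, and previous antibiotic exposure" and are defined as "controls as preterm neonates who do not develop any clinical or culture proven sepsis during the observation period (after 72 hours of life"). The sample size compares the proportion of children with dysbiosis, 30% without LOS and 60% with LOS, at 42 per group.
- **Variables to predict LOS and gut dysbiosis:** stool is "collected in a standardized manner on day 1–3, and days 7, 14, 21 (each ±3"). Type of feeding is recorded for the 24 hours before, so it changes over time.
- **Blood cultures** and **Isolation and identification:** cultures must not hold up antimicrobial treatment, an episode is classed as culture-proven or clinical with the help of the culture result, and bottles are "monitored for a maximum of five days to observe bacteria growth".

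**The concern.** The primary question is whether dysbiosis comes before LOS, so the comparison needs case and control samples from the same stretch of life. Three stated rules work against this when taken together.

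1. The exclusion can only remove case samples. A control contributes its full series, including ages that its matched case never reached free of LOS.
2. Postnatal age is not a matching factor, and a control has no date at which earlier antibiotic exposure or feeding type is to be read. A control can therefore be matched on antibiotics or feeding that arose after the case's onset age.
3. The cut-off is the diagnosis, which is not dated. It could mean clinical recognition, culture draw or culture result. Treatment may start well before the result, and the Statistical analysis section itself expects antibiotics to change the microbiome strongly.

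At stake is the contrast on which the study is powered: a per-child proportion that can differ between groups because of age at sampling and number of samples alone.

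**Working it through.** **1. The plan's own figure.** Inputs: p1 = 0.30, p2 = 0.60, two-sided alpha 5%, power 80%, 1:1.

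- Pooled variance under the null: n = [1.960·√(2·0.45·0.55) + 0.842·√(0.21 + 0.24)]² / 0.30² = 41.97, so 42 per group. This reproduces 84.
- Unpooled: 7.849·0.45/0.09 = 39.2, so 40 per group.

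The powered contrast is therefore a proportion of children, not a mean species abundance.

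**2. Samples kept, by hand.** Take nominal days 2, 7, 14 and 21. Assume onset uniform on days 3–28.

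- Fraction of cases keeping each sample: 1, 21/25 = 0.84, 14/25 = 0.56, 7/25 = 0.28. The sum is 2.68 samples per case.
- Mean age of kept samples: (2·1 + 7·0.84 + 14·0.56 + 21·0.28)/2.68 = 21.6/2.68 = 8.1 days.
- Controls: 4 samples, (2 + 7 + 14 + 21)/4 = 11.0 days.

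**3. The same with sampling windows.** Samples uniform in days 0–3, 4–10, 11–17 and 18–24. Onset (assumed) uniform on days 3–28, or triangular on that range.

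| Onset | Samples per case | Mean age, cases | Any abnormal sample, cases |
|---|---|---|---|
| Uniform | 2.68 | 7.7 d | 21% |
| Peak day 10 | 2.45 | 6.5 d | 19% |
| Peak day 14 | 2.64 | 7.0 d | 21% |
| Peak day 17 | 2.78 | 7.5 d | 22% |
| Controls | 4 | 10.9 d | 30% (set) |

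The last column assumes that a child is dysbiotic if any sample is, with equal and independent risk per sample. Setting controls at 30% gives a per-sample risk of 1 − 0.7^(1/4) = 0.085. A child with k samples then has probability 1 − 0.7^(k/4), which is 8.5%, 16.3%, 23.5% and 30.0% for k = 1 to 4. These are averaged over the cases' distribution of k. Earlier onset (day 3 plus an exponential with mean 6 days, nominal sampling days) gives 1.7 samples at 5.1 days and 14%, but fits less well with the Introduction's peak between the second and third week.

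**4. Does the age term rescue the species model?** Null simulation: 54 cases, 54 controls, 60 runs per scenario, a linear or saturating age trend, two onset distributions, random intercept per child.

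- Without age: LOS coefficient biased by −0.26 to −0.46 residual SD, 45–83% false positives.
- With days of life: bias −0.002 to −0.033, 3–7% false positives. With 60 runs the standard error at a 5% rate is √(0.05·0.95/60) = 2.8 points, so this is compatible with 5%.

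For species abundances, then, the stated model largely handles age and unequal numbers of samples under these assumed trends.

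**5. The date of diagnosis.** If diagnosis is dated at the culture result, a case has a post-onset sample counted as preceding when a sample falls between onset and result. With the windows and onset distributions of step 3:

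- 2-day lag: 24–27% of cases.
- 5-day lag: 52–62% of cases.

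Dividing the lag by seven days would give 29–71%, which is too high because sampling ends by day 24. If diagnosis means clinical recognition, the lag largely disappears.

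**The case against.** The strongest reply is that the exclusion rule and the days-of-life term belong to the same analysis. Age is adjusted for, the mixed model tolerates unequal series, and step 4 shows almost no remaining bias. That stands. A reader might infer that the whole pre-LOS comparison is confounded by age and sample number; the documents do not support this for species abundances.

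A second reply is that the article describes no test of per-child dysbiosis proportions, and that the definition of dysbiosis and its window may sit in the full protocol or analysis plan. The fixed schedule also allows comparison at the same visit. This is partly right, and the missing definition is not itself the complaint. But the article does fix the matching set, the control definition and a cut-off that can act only on cases, and it bases the sample size on that proportion. These stated pieces do not fit together, and an age term in another model neither repairs the proportion nor says when a control's antibiotic exposure counts.

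Third, the shift from 30% to 19–22% depends on an assumed any-sample definition, and it lowers the case proportion. A reader might infer a spurious finding in favour of the hypothesis; in this illustration the bias runs the other way. The expected 54–101 complete sets against 42 needed give some reserve of power.

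Fourth, the lag figures need diagnosis to mean the culture result. The article nowhere says so. Its rationale places antibiotics after diagnosis, and the LOS definition rests on clinical signs judged by physicians, both of which favour an earlier date. Five days is also the maximum incubation, not the usual time to a positive result. The documents therefore do not support saying that post-onset samples will enter the preceding set, only that the wording leaves this open.

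**Conclusion.** The point holds in a limited form. The cut-off truncates cases only, controls have no index age, and matching omits postnatal age while using two factors that change over time. For mean species abundances, the planned age-adjusted mixed model deals with most of this, provided the age trend is modelled adequately. What remains exposed is the powered per-child contrast of 30% against 60%, and the matching on previous antibiotics and feeding.

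The imbalance is about 2.5–2.8 samples at 6.5–7.7 days in cases against 4 at 10.9 days in controls, assuming onset on days 3–28 and no missed samples. Its effect on the dysbiosis proportion depends on how a child is classified; under the any-sample illustration it works against the hypothesis and costs power. The undated diagnosis could affect roughly 24–62% of cases, conditional on a 2–5 day lag to the culture result, and few if it means clinical recognition. It should be settled before controls are selected and analysed, because it bears on the primary question and costs little.

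**What to change.** - Define the case index time as the earliest of symptom onset, culture draw or start of antibiotics for the episode. This serves the analysis only and changes no clinical procedure.
- Give each matched control its case's postnatal age at that time as index age, and require the control to be alive and under follow-up then.
- For the case-control dysbiosis comparison, use only samples before the index age in both groups, and assess feeding type and antibiotic exposure up to that age.
- Keep the age-adjusted mixed model for species abundances, cutting case samples at the same index time.

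The cost is protocol or analysis-plan wording and programming; no new samples are needed. The downside is small: later control samples leave the matched comparison but stay available for the mixed model and for descriptive trajectories.
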